## Abstract

**Background:**

The high incidence of cardiovascular disease in patients with end stage renal disease (ESRD) is related to the accumulation of uremic toxins in the middle and large-middle molecular weight range. As online hemodiafiltration (HDF) removes these molecules more effectively than standard hemodialysis (HD), it has been suggested that online HDF improves survival and cardiovascular outcome. Thus far, no conclusive data of HDF on target organ damage and cardiovascular morbidity and mortality are available. Therefore, the CONvective TRAnsport STudy (CONTRAST) has been initiated.

**Methods:**

CONTRAST is a Dutch multi-center randomised controlled trial. In this trial, approximately 800 chronic hemodialysis patients will be randomised between online HDF and low-flux HD, and followed for three years. The primary endpoint is all cause mortality. The main secondary outcome variables are fatal and non-fatal cardiovascular events.

**Conclusion:**

The study is designed to provide conclusive evidence whether online HDF leads to a lower mortality and less cardiovascular events as compared to standard HD.

## Background and rationale

Atherosclerotic cardiovascular disease (CVD) is common among hemodialysis (HD) patients. In fact, approximately 50% of the deaths is attributed to cardiovascular causes, which is much higher than in the general population [1]. In addition, chronic HD patients suffer from atherosclerotic complications at a relatively younger age and die younger from ischemic heart disease [2]. The origin of CVD in chronic HD patients is most probably multi-factorial, as the extremely high prevalence in this patient group is not easily explained by traditional risk factors, either alone or in combination [3]. In recent years, other contributing factors have emerged, including the accumulation of uremic toxins, disturbances in the immuno-inflammatory system, as reflected by a chronic micro-inflammatory state, increased oxidative stress, and endothelial dysfunction [4-6]. In particular the retention of larger uremic toxins, the so-called middle molecules (MM, molecular weight [MW] 0.5 – 50 kDa), may play an important role in the pathogenesis of CVD [7,8]. Therefore, it is conceivable that dialysis modalities with superior MM removal reduce CVD and improve survival.

In contrast to diffusive dialysis strategies, which mainly remove small MW solutes, such as urea and creatinine, convective dialysis strategies are particularly effective in the removal of larger molecules. In hemodiafiltration (HDF), diffusive and convective transport are combined, providing an optimal removal of both small and larger MW substances up to the range of 30 – 40 kDa. Clinical studies have shown that beta-2-microglobulin (β2 m), which is a typical MM with a MW of 11.8 kDa and therefore incapable of passage through the membrane of low flux devices, is effectively removed during HDF leading to lower pre-dialysis levels in the long term [9,10]. Similarly, the removal of other MM such as advanced glycation end-products (AGEs), leptin, and complement factor D is enhanced by convective transport [11-13]. Apart from the increased MM clearance, it has been suggested that HDF improves the removal of smaller molecules that are highly protein bound, due to a better elimination of the unbound fraction [14]. With respect to homocysteine, which is >90% protein bound, the observed decrease may also be explained by an improved removal of uremic substances with inhibitory effects on its metabolism [15]. Finally, it has been shown that treatment with online HDF leads to lower plasma phosphate concentrations, as compared to standard HD [16,17].

At present, it is unclear whether HDF has a favourable effect on the micro-inflammatory state in dialysis patients. Although a reduction of pro-inflammatory proteins has been shown during HDF [18], anti-inflammatory cytokines may also be removed. Of note, besides solute removal, other factors may influence the inflammatory-state as well, such as the bio-incompatibility of the dialyser membrane and the microbiological quality of the dialysate [19,20]. Considering oxidative stress and endothelial dysfunction, data on the effects of HDF on these parameters are limited.

In summary, compared to standard HD, HDF improves the uremic state by an increased clearance of MM and other, mainly protein bound, uremic toxins. Circumstantial evidence implies that these effects result in less vascular damage and ultimately in decreased cardiovascular morbidity and mortality (figure 1). Although observational studies suggest that online HDF improves cardiovascular outcome in chronic HD patients [21,22], two small randomised studies failed to show any differences between online HDF and standard HD [23,24]. However, the latter analysis lacked adequate power to detect differences in clinical endpoints.

**Figure 1 F1:**
[figure not shown]
Hypothesis

Based on the above-mentioned theoretical considerations, the scarcity of reliable clinical data, and the growing interest in convective techniques under nephrologists, the CONvective TRAnsport STudy (CONTRAST) has been initiated. CONTRAST is a randomised controlled trial investigating the effects of online HDF on clinical endpoints, compared to low-flux HD. If online HDF indeed leads to an improvement in CV morbidity and mortality, this finding will imply a breakthrough in the treatment of chronic HD patients.

## Methods

### Objectives

The primary objective of CONTRAST is to assess the effect of on-line HDF on all cause mortality, when compared to standard low-flux HD. The main secondary outcomes are fatal and non-fatal cardiovascular events. Other secondary outcome measures include differences between treatment regimens on the progression of left ventricular mass index (LVMi), as assessed by echocardiography, the progression of atherosclerosis as assessed by measurement of carotid intima-media thickness (CIMT) and the progression of arterial stiffness, as assessed by measurement of aortic pulse wave velocity (PWV). Furthermore, several laboratory markers of endothelial function, inflammatory state, and oxidative stress will be assessed over time and compared between the two treatment groups. In addition, subjective global assessment (SGA) is performed in the study patients as a measure of nutritional state, and a questionnaire is used to investigate the effects of on-line HDF on quality of life.

### Study design

In this randomised controlled trial, participants are randomised centrally into a 1:1 ratio for treatment with online HDF or treatment with low-flux HD. Randomisation is stratified by the participating centres and occurs in blocks. The follow-up period is three years. At present, 24 dialysis centres have agreed to recruit the required number of patients. The study is conducted according to good clinical practice (GCP) guidelines.

#### Patients

The in- and exclusion criteria are given in table 1. Since the study results may be of importance for chronic HD patients of all ages, no upper age limit has been set. Severe incompliance is defined as non-adherence to the dialysis prescription, especially the frequency and duration of dialysis treatment. Permission for participation in other (e.g. observational) studies will be discussed with and decided by the executive committee.

**Table 1 T1:** Inclusion and exclusion criteria

**Inclusion criteria**
patients treated by HD 2 or 3 times a week, for at least 2 months.
patients able to understand the study procedures.
patients willing to provide written informed consent.

**Exclusion criteria**

current age < 18 years
treatment by HDF or high flux HD in the preceding 6 months
severe incompliance
life expectancy < 3 months due to non renal disease
participation to other clinical intervention trials evaluating cardiovascular outcome

#### Stabilisation period

Before randomisation, patients will be dialysed 3 times (or 2 times) per week with low-flux synthetic dialysers (UF-coefficient < 20 ml/mmHg/h) for at least 6 months in case of a prevalent dialysis patient and at least 2 months in case of a new dialysis patient.

Blood flow will be maintained at 250–400 ml/min. Anticoagulation is performed with low molecular weight heparin (LMWH) before HD. Patients on coumarins receive 50% of the LMWH dose. Treatment times will be adapted to a target dialysis spKt/V urea of ≥ 1.2 per treatment. Ultra pure water is used for preparation of dialysis fluid. Bicarbonate is provided from powder cartridges to avoid the risk of a bacterial load from bicarbonate concentrates. For instance, the biBAG^R ^system (Fresenius) and BiCart^R ^system (Gambro) will be used. The dialysate flow is 500 ml/min and the temperature of the dialysate is 36°C.

#### Routine patient care

Metabolic control will be performed according to the guidelines of the Quality of Care Committee of the Dutch Federation of Nephrology. Anti-hypertensive medication, lipid lowering therapy, platelet aggregation inhibitors and medication to treat renal anemia and renal osteodystrophy will also be prescribed according to these guidelines, and, if not available, according to usual care.

#### Randomisation

The patients will be randomised as soon as they are considered to be stable. When a patient has been randomised for low-flux HD, the treatment as performed in the stabilisation period will be continued. Treatment times will be adjusted only if dialysis spKt/V urea < 1.2 per treatment or if ultrafiltration goals can not be achieved, according to the attending nephrologist. When randomised for online HDF, patients will be treated with a target post-dilution dose of 6 l/h (~100 ml/min) and a high-flux synthetic dialyser (UF-coefficient > 20 ml/mmHg/h). Blood flow will be set at >300 ml/min, if possible, in order to achieve a substitution volume of 100 ml/min. If the blood flow is less than 300 ml/min, the post-dilution volume will be decreased accordingly (filtration and post-dilution <25–33% of blood flow). If necessary, the dose of LMWH will be increased and given in two separate doses. Treatment times will be fixed according to the prescription in the stabilisation period and adjusted only when spKt/V urea is < 1.2 / treatment. Metabolic control and medication is similar to the low-flux group, as described above.

#### Dialyser membranes

Dialysers with comparable biocompatible membrane material and surface area will be used in both treatment groups, to ascertain that differences in clearance result from differences in convective transport, rather than differences in dialyser characteristics. Only if the target dose of 6 l/h post-dilution is not achieved in the online HDF patients, it is allowed to prescribe a membrane with a larger surface area. The membranes advised by the study group are summarised in table 2. As many low-flux membranes with a membrane surface > 1.5 m^2 ^have a UF coefficient 10–20 ml/mmHg/h, in this study low-flux is defined as a UF coefficient of < 20 ml/mmHg/h.

**Table 2 T2:** Dialyser characteristics for both treatment arms

	**Low-flux HD**		**Online HDF**	
**Company**	Gambro	Fresenius	Gambro	Fresenius
**Dialyser**	Polyflux 17L	F8HPS	Polyflux 170H	FX80
**Membrane material**	polyamide	polysulfone	polyamide	polysulfone (helixone)
**Sterilisation method**	heat	heat	heat	heat
**Surface area (m^2 ^)**	1.7	1.8	1.7	1.8
**Membrane thickness (μm)**	50	40	50	35
**UF coefficient (ml/mmHg/h)**	13	18	65	59
**In vitro clearance:**^# ^				
**Urea**	260	251	268	276
**Phosphate**	198	193	229	239
**Vit B12**	111	118	158	175

# (QB = 300 ml/min, QD = 500 ml/min)

#### Online HDF technique

During hemodiafiltration, the removal of larger solutes is increased by excess ultrafiltration, leading to solute removal by convection. As fluid removal exceeds the desired weight loss of the patient, fluid balance is maintained by the infusion of a pyrogen-free substitution solution. In addition, dialysate is used to create a concentration gradient for solute removal by diffusion, as in standard HD. At the introduction of HDF more than 20 years ago, the substitution fluid was supplied in bags. The infusion volumes were limited due to the high costs and laborious procedure, limiting the efficiency of HDF.

In recent years, however, technical advances have made it possible to prepare the substitution solution online from ultra pure water and dialysate concentrates. As a result, the volume of the substitution fluid could be increased considerably, without the disadvantages of inconvenient bags. Hence, the UF rate can be increased up to 50L per treatment in the pre-dilution mode and 25L in the post-dilution mode [25].

#### Online dialysate and substitution fluid preparation

Ultra-pure water is used for the preparation of bicarbonate-containing dialysis fluid, which undergoes one step of ultrafiltration converting it into ultra pure dialysis fluid. Dialysis fluid is produced at a rate of 600–800 ml/min of which approximately 100 ml/min is diverted for further processing into substitution fluid. The electrolyte composition of the dialysis fluid is: Na^+ ^138–140 mmol/l; K^+ ^1.0–3.0 mmol/l; HCO_3 _^- ^30–35 mmol/l; Ca^++ ^1.0–1.7 mmol/l; Mg^++ ^0.5 mmol/l; Cl^- ^108–109.5 mmol/l; glucose 0–5.6 mmol/l; acetate 3 mmol/l.

The substitution fluid is prepared from the dialysis fluid by one additional step of controlled ultrafiltration, before it is infused post-filter into the blood. The electrolyte composition of the substitution fluid is the same as the composition of the dialysis fluid. Ultrafiltration procedures will be performed according to the manufacturers' instructions, as described below.

- The on-line system, ONLINEplus™ (Fresenius Medical Care, Bad Homburg, Germany) is integrated into the dialysis machine (4008 series; Fresenius Medical Care) and consists of two ultrafilters (DIASAFE^® ^plus), an infusate pump module, and disposable infusate lines. Infusate is prepared continuously by double-stage ultrafiltration. Both filters are subjected to automated membrane integrity tests before dialysis, and are replaced after 100 treatments or 12 weeks of use, whichever comes first. Dialysis fluid downstream from the first filter stage enters the dialyser; part of the stream is subjected to cross-flow filtration in the second filter in order to produce infusate. The infusate stream is connected with the venous bubble catcher for post-dilution HDF [25,26].

- The AK 100/200 ULTRA dialysis machine (Gambro AB, Lund, Sweden) prepares ultra pure water and ultra pure dialysis fluid by stepwise ultrafiltration of water and bicarbonate -containing dialysis fluid (BiCart) using two polyamide ultrafilters (U8000 S). When used for HDF, sterile non-pyrogenic solution is prepared on-line from the ultra pure dialysis fluid by an additional step of ultrafiltration using a sterile polyamide ultrafilter (U2000) integrated in a sterile line set (Steriset). The hygiene of the fluid pathway, including the U8000S ultrafilters, will be assured by heat disinfections after each treatment. The U8000S filters are changed bimonthly. The final ultrafilter (U2000) is employed on a single-use basis [26,25].

### Data collection

#### Baseline and follow-up data registration

At baseline, all relevant information will be documented: i.e. demographical data, information on cardiovascular risk factors, time on dialysis, cause of renal insufficiency, and medication. A follow-up visit will be scheduled every three months. During this visit, the occurrence of CV events, death, and hospitalisation will be documented. In addition, blood pressure, body weight and the achieved filtration and substitution dose per treatment will be registered. Case record forms are provided using the TeleForm system (version 8.1.1, Cardiff Software Inc, Vista, CA, USA). As all completed forms are scanned, no data entry by typing is needed. Registration of all data will be performed in each centre by the attending nephrologists and research nurses.

#### Recording outcome events

CV events include fatal or non-fatal myocardial infarction, stroke, therapeutic coronary procedure (PTCA or stenting), therapeutic carotid procedure (endarterectomy or stenting), and PTA and vascular intervention (revascularisation, PTA or stenting). Congestive heart failure is excluded as a CV event, since the discrimination with fluid overload is often hard to make in chronic HD patients. Furthermore, hospitalisations, duration of the hospitalisations and main diagnosis (including the occurrence of infections) will be recorded during the study period.

An independent event committee will evaluate all causes of death, cardiovascular events, and infections. The primary investigators will collect sufficient information of the events for the event committee. The event committee is blinded for information on the received treatment and consists of physicians with different specialisations: neurologists, vascular surgeons, nephrologists, internists, and cardiologists. Events will be coded as fatal and non-fatal, definite, probable and possible and not codeable (i.e. insufficient information). Only definite and probable events will be used in the final analysis. This procedure is successfully applied in a number of studies coordinated by the Julius Center, e.g. in the SMART study [27].

#### Left ventricular hypertrophy

Using transthoracic M-mode echocardiography from the parasternal long axis position, left ventricular end-diastolic diameter (LVEDD), end-systolic diameter (LVESD) as well as posterior and septal wall thickness will be determined at baseline, after 6 months, after 12 months and annually afterwards, on a midweek non-dialysis day according to a central uniform protocol. From these parameters left ventricular ejection fraction (LVEF) will be determined as LVEDD – LVESD/LVEDD, while the left ventricular mass index (LVMi) will be calculated using the formula of Devereux and Reichek [28], modified in accordance with the recommendations of the American Society of Echocardiography [29]. The ultrasound investigations will be recorded on a compact disc and analysed off-line by experienced cardiologists in a core laboratory.

#### Vessel wall measurements

With respect to carotid intima-media thickness (CIMT), the outcome is the change in mean common CIMT, defined as the average of the intima-media thickness measurements performed circumferentially at pre-defined angles for the near and far wall of 10 mm segments of the right and left distal common carotid arteries [30]. A limited number of centres will be involved in the CIMT measurements in this study. Centres will be trained according to a central uniform carotid ultrasound protocol. Before actually starting the study, sonographers need to be certified as outlined in the CIMT ultrasound protocol.

Measurements will be performed at baseline and then annually on a midweek non-dialysis day. The ultrasound scan is being recorded on videotape and analysed off line by a core laboratory. Quality Assurance and Quality Control procedures as existing and applied in several (inter)national trials will be implemented [31,32].

Pulse wave velocity (PWV) is determined to provide additional information on functional changes of the arterial wall [33]. The outcome measurement is the change in aortic PWV. A limited number of centres will be involved in the PWV measurements in this study. Centres will be trained according to a central uniform PWV protocol. Data are checked regularly on quality control aspects as defined in the PWV protocol as described earlier [34].

Measurements will be performed at baseline and then annually on a midweek non-dialysis day.

#### Nutritional state

At base-line, after 1, 2 years and at the end of the study, nutritional state is assessed by subjective global assessment (SGA), pre-albumin and dry weight [35].

#### Quality of life

Patient well-being will be estimated at baseline, and once a year by the Kidney Disease Quality of Life Short Form (KDQOL-SF). This version is validated in American and Dutch dialysis patients [36,37].

#### Laboratory assessments

Three monthly, blood samples will be drawn for routine laboratory assessments. In addition, blood samples will be taken at baseline, and after 6, 12, 18, 24, and 36 months for determinations of oxidative stress, inflammatory and endothelial function markers. Finally, a whole blood sample will be stored for future research on the effect of genetics on the response to HDF, after specific permission of the patients in the informed consent form.

### Statistical methods

The results of the study will be analysed according to the 'intention to treat' principle.

#### Primary outcome

The primary outcome variable is the time until the occurrence of an event defined as 'all cause mortality'. Results will be presented as Kaplan-Meier curves for the two treatment arms and the difference between the two treatments will be analysed using a log-rank test. The log-rank test will be adjusted for the effect of cumulative data analyses (see below).

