#### Secondary outcomes

CV events are considered as secondary outcome variables. They will be analysed and presented as described for the primary outcome variable.

The primary analysis of CIMT progression will employ a linear random coefficient (Laird-Ware) model using real visit days, treatment and clinical center as independent variables. for each participant, the intercept and slope of CIMT change over time is assumed to be a normally distributed random variable with different means for the two treatment groups. The mean slope for the HDF treatment group will be compared to that for the low flux group using linear contrasts and a 5% significance level. Additional exploratory analyses will evaluate the impact of including baseline CIMT, lumen diameter, and ultrasound reader as additional co-variates.

The data analytic approach to arrive at the PWV outcome variable and the LVMi outcome variable is similar to that of the CIMT outcome. Adjustments that will be taken into account in the estimates are changes in MAP and changes in heart rate, since both are closely related to PWV.

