#### Sample size considerations

The sample size of the present study is based on the following event rates: the 3-year all cause mortality rate among subjects with ESRD is 44% based on data from the Dutch renal replacement registry (RENINE) [38]. CV mortality constitutes 40–60% of the total group of deaths, leading to a 3 year CV mortality rate of 22% in HD patients. Assuming that the incidence of non-fatal CVD is equal to the CV mortality rate (22%), the three-year incidence of fatal and non-fatal CVD is 44%. In addition, based on experience ± 8% of the ESRD patients will undergo renal transplantation yearly and as such is being censored in the trial.

Assuming that HDF will reduce all cause mortality with 20%, it has been estimated that with a two-sided alpha of 0.05 and a power of 80%, about 772 patients need to be enrolled and followed for three years. In these patients about 250 events are expected to come to a decision. Note that the total number of patients to be included cannot be specified in advance because of the planned sequential interim analyses, as described below.

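### Randomisation is stratified by centre, but the log-rank tests for mortality and cardiovascular events, and the sequential Z and V, are described without centre strata: a modest loss of efficiency if centres differ

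*Protocol article*

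**What the plan says.** - **Allocation** (Study design): "participants are randomised centrally into a 1:1 ratio", and "Randomisation is stratified by the participating centres and occurs in blocks". The same section states that "24 dialysis centres have agreed to recruit the required number of patients".
- **Primary test** (Primary outcome): "the difference between the two treatments will be analysed using a log-rank test". One adjustment is named: "The log-rank test will be adjusted for the effect of cumulative data analyses".
- **Cardiovascular events** (Secondary outcomes): "They will be analysed and presented as described for the primary outcome variable".
- **Sequential statistics** (Interim analysis): Z is the observed minus the expected number of control-group events, and V is about a quarter of all events. Strata are not mentioned.
- **CIMT** (Secondary outcomes): a random coefficient model "using real visit days, treatment and clinical center as independent variables". Pulse wave velocity and left ventricular mass index follow a similar approach.

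Centre is therefore used in the allocation and in the imaging models. It does not appear in the description of the test that decides the trial.

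**The concern.** Blocking within centre gives the two arms nearly the same mix of centres. If death rates differ between centres, part of the variation in outcome is then balanced by design and cannot contribute to chance differences between the arms. A log-rank test that ignores centre still counts that part in its variance. The standardised statistic is then too small on average, and the true error rate falls below the nominal 5%. The marginal hazard ratio is also pulled towards 1 relative to the within-centre ratio.

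At stake is some of the power that the design aims for "with a two-sided alpha of 0.05 and a power of 80"%. Treatment effects are not made to look larger, and the false-positive rate is not raised.

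**Working it through.** **Inputs from the article.** Three-year control survival 0.56 and HDF survival 0.648 (Interim analysis); transplantation about 8% a year, censored; three years of follow-up; about 772 patients (Sample size considerations); 24 centres, 1:1, blocked (Study design).

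**Assumed.** 768 patients (24 × 32, the nearest multiple to 772), blocks of 4, exponential survival, and normally distributed centre effects on the log hazard with SD 0 to 0.8. The article gives no figure for this SD.

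**Step 1: rates.**
- Control hazard = −ln(0.56)/3 = 0.193 per year.
- Hazard ratio = ln(0.648)/ln(0.56) = 0.748, which agrees with the article's 0.75.
- Transplant hazard = −ln(0.92) = 0.0834 per year.
- Proportion with an event by three years = λ/(λ+μ) × [1 − exp(−3(λ+μ))], where λ is the death hazard and μ the transplant hazard. This gives 0.394 (HD) and 0.314 (HDF), mean 0.354, so 768 × 0.354 = 272 deaths.

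**Step 2: anchor for the simulation.** With 272 events and a single test at 1.96, power = Φ(√272/2 × 0.29 − 1.96) = Φ(0.43) = 67%. The simulation with no centre differences gives 66.5%, so it behaves as expected.

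**Step 3: plain against centre-stratified log-rank test.** There were 5,000 simulated trials per cell, critical value 1.96, and the base hazard was reset so that mean control survival stays at 0.56. Unequal centres means six each of 8, 16, 32 and 72 patients. Each cell shows plain / stratified.

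| Centre SD | Alpha, equal | Power, equal | Alpha, unequal | Power, unequal |
|---|---|---|---|---|
| 0 | 5.3 / 5.1% | 66.5 / 65.8% | 4.9 / 4.8% | 66.6 / 65.8% |
| 0.2 | 4.4 / 4.6% | 65.6 / 65.4% | 4.7 / 4.9% | 66.1 / 66.1% |
| 0.3 | 5.1 / 5.3% | 65.4 / 66.5% | 4.5 / 4.8% | 65.0 / 66.0% |
| 0.5 | 4.2 / 5.1% | 64.6 / 68.1% | 4.0 / 5.2% | 62.8 / 66.3% |
| 0.8 | 3.5 / 5.7% | 55.7 / 66.1% | 3.1 / 4.9% | 55.8 / 65.9% |

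The Monte Carlo standard error is about 0.3 points for alpha and 0.7 for power. Two further runs at SD 0.5 gave alpha 4.1 / 5.2% with power 63.3 / 66.3%, and alpha 3.7 / 4.7% with power 64.7 / 68.6%. The loss at SD 0.5 is thus 3.0 to 3.9 points.

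**Step 4: what the SDs mean.** The middle 95% of centres span hazard multipliers exp(±1.96 × SD), and three-year mortality is 1 − 0.56^multiplier, with the median centre at 0.193 per year.
- SD 0.2: 0.68 to 1.48, mortality 32% to 58%.
- SD 0.3: 0.56 to 1.80, mortality 28% to 65%.
- SD 0.5: 0.38 to 2.66, mortality 20% to 79%.

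**Step 5: cost of stratifying.** With no centre differences, power falls by 0.1 to 0.8 point across runs. At full size (32 per centre) V is about 1.5% lower than without strata. At about 144 patients (6 per centre on average) V is about 6% to 18% lower, depending on the follow-up reached and the spread over centres.

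**The case against.** The strongest reply is that the article is condensed and never says the test is unstratified. Strata are often left to an analysis plan, and the definition of Z does not exclude a sum over centres. The adjustment for cumulative analyses is the one that is named, but it is not said to be the only one. The CIMT contrast can also be explained: the section Vessel wall measurements says that CIMT is done in a limited number of centres, where a centre term may absorb measurement differences that have no counterpart for death.

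This stands in part. The article does not contradict itself, and a reader should not infer that it commits to an unstratified test. What remains is that the decisive test and its sequential statistics are described, with one adjustment named, and the randomisation factor is left out. Analysing by the groups used to randomise is a specific improvement to that description.

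The objection to the size also has force. SD 0.5 implies roughly a sevenfold range of hazard between centres (2.66/0.375 = 7.1). The article describes common dialysis conditions and national guidelines, which gives no reason to presume so wide a spread. At SD 0.2 to 0.3 the gain is close to simulation error.

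Finally, sparse early looks do not favour stratification. The database goes to the monitoring board every two months, and just over 150 patients had been included by April 2005.

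**Conclusion.** The point holds as a moderate-confidence, inexpensive improvement. If centres differ materially in mortality, the log-rank test as described is mildly conservative: at an assumed SD of 0.5, alpha is about 4% and about 3 to 4 points of fixed-sample power are lost. At 0.2 to 0.3 the loss is about 1 point or less, and at 0 there is none. At 0.8 it would be about 10 points, but nothing in the document supports so large a spread.

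Three stronger readings are tempting, and the document supports none of them.

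- **That the result would be invalid or biased towards HDF.** The error is on the conservative side. Attenuation of the hazard ratio is expected in principle but was not quantified here.
- **That the trial is under-powered, because the table shows 65% to 68%.** Those are fixed-sample powers at about 272 to 279 events and serve only to compare two tests. The planned design is a sequential double triangular test. Simulated with θ = 0.29, it gives power of about 0.81 at a mean of about 254 events, in line with the article's figure of about 250. The article also leaves total enrolment open.
- **That the same loss arises at every interim look.** The sequential procedure was not simulated with strata, and at sparse early looks stratifying itself gives up information.

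**What to change.** State in the statistical methods:

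1. Mortality and cardiovascular events are compared with a log-rank test stratified by centre.
2. The sequential Z and V are the sums over centres of the within-centre values.
3. Centres below a stated size are pooled by a rule fixed without reference to unblinded results, preferably before the first unblinded look. If looks have already taken place, the rule should be set by people who have not seen the results by arm.
4. The hazard ratio comes from a Cox model stratified by centre.

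If the full protocol or analysis plan already stratifies, one sentence saying so is enough.

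The change is to the analysis text and the interim program, including the pooling rule. Patients, visits and the planned sample size are unaffected. The statistical price is under about 1 point of power if centres do not differ, and a slower build-up of V while centres are small. The pooling rule limits the latter.
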